## Abstract

Supplemental Digital Content is available in the text

## Background

1

### Background and rationale

1.1

Sepsis remains a challenge in intensive care medicine, its incidence increasing continuously over the past decades.^[1–3]^ Despite massive efforts in sepsis research, new therapeutic approaches are rare and mortality in patients with septic shock still remains unacceptably high.^[1–3]^ In addition to an early focus control, recent guidelines recommend the initiation of an empiric antibiotic therapy as early as possible (preferably within 1 hour) following diagnosis of sepsis.^[4]^ However, the identification of the causative pathogen is crucial for early optimization of the antimicrobial treatment regime. In this context, culture-based diagnostic procedures (e.g., blood cultures) represent the standard of care, although they are associated with relevant limitations^[4,5]^: (i) depending on microbiological growth, it might take up to several days until final results (including pathogen identification and resistance patterns) are available, (ii) culture-based diagnostic procedures often reveal false negative results due to the administration of an empiric antibiotic therapy, and (iii) may however also reveal false positive results due to microbial contaminations (e.g., not strictly aseptic blood sample collection). Accordingly, patients suffering from sepsis or septic shock are at high risk for antimicrobial overtreatment, antibiotics-related toxicity, and the selection of multidrug-resistant pathogens due to an inadequate and prolonged use of broad-spectrum antibiotics. In this context, culture-independent molecular diagnostic procedures [e.g., polymerase chain reaction (PCR)-based techniques] have already been introduced for the identification of the causative pathogen in infected patients.^[6–10]^ However, the occurrence of ambiguous results as well as limitations in the quantitative measurement of the bacterial load in patients’ samples and detection of antibiotic resistance markers are known limitations of these PCR-based diagnostic approaches. Therefore, the concept of an unbiased sequence analyses of circulating cell-free deoxyribonucleic acid (cfDNA) from plasma samples of septic patients by next-generation sequencing (NGS) has recently been identified to be a promising diagnostic platform for critically ill patients suffering from bloodstream infections.^[11,12]^ This new NGS-based approach provides a basis to differentiate the relevant infecting organisms and to rule out potential microbial contaminants (e.g., coagulase-negative staphylococci) by establishing a quantitative score [sepsis indicating quantifier (SIQ) score]. This goes beyond state-of-the-art molecular approaches for the diagnosis of infecting organisms in septic specimens, which are not open but instead based on PCR amplification of defined targets and are, in most cases, just qualitative in nature. Therefore, this approach allows for an unbiased analysis of bloodstream infections, which might be especially useful for the diagnosis of cases where classic microbiological or molecular diagnostic approaches fail. However, although this new approach might be more sensitive and specific than state-of-the-art technologies, additional clinical trials are needed to exactly define the performance as well as the clinical value, as the presented studies were limited by the low number of patients.

### Question and justification of the project (rationale)

1.2

The objective of this prospective, observational, noninterventional, multicenter study on the diagnostic use of NGS in patients suffering from sepsis is conducted to provide evidence of the effectiveness of a NGS-based approach in the quantitative measurement of the bacterial load in patients’ blood samples-a clinical trial on a new technique in an old diagnostic problem field.

### Objectives

1.3

*Next GeneSiS* primarily evaluates the performance of a NGS-based approach for the detection of the relevant infecting organisms in patients with suspected or proven sepsis by the use of the quantitative sepsis indicating quantifier (SIQ) score in comparison to standard (culture-based) microbiological diagnostics. Secondarily, the clinical value of this approach will be estimated by a panel of independent clinical specialists, retrospectively identifying potential changes in patients’ management based on NGS results.

The following aspects have been defined as further secondary objectives:(1)Evaluation of antimicrobial resistance patterns and virulence factors;(2)Evaluation of process times for NGS-based measurements;(3)Diagnostic or prognostic value of host nucleosome positioning patterns derived from plasma cell-free DNA in patients with suspected or proven sepsis;(4)Diagnostic value of host expression profiles including RNA-derived biomarkers in patients with suspected or proven sepsis;(5)Diagnostic or prognostic value of methylglyoxal (MG)-derived carbonyl stress in patients with suspected or proven sepsis.

### Trial design

1.4

*Next GeneSiS* is a prospective, observational, noninterventional, multicenter study.

This study protocol follows the Standard Protocol Items: Recommendations for Interventional Trials (SPIRIT) guidelines (see Supplemental File 1).

## Methods

2

### Study setting

2.1

*Next GeneSiS* is conducted in terms of a multicenter study on medical as well as surgical intensive care units (ICUs) of maximum care hospitals throughout the *Translational Intensive Care Research Network on Organ Dysfunction* (TIFOnet) in Germany. Coordinating center of the study is the Department of Anesthesiology, Heidelberg University Hospital supported by the Coordination Centre for Clinical Trials (KKS) Heidelberg. Data management and statistical analysis are provided by the Institute for Medical Biometry and Informatics (IMBI), Heidelberg. Fraunhofer IGB provides next-generation sequencing (NGS) devices and is responsible for NGS-based measurements as well as calculation of the SIQ score in plasma samples of included septic patients.

### Eligibility criteria

2.2

Patients with sepsis or septic shock according to the new sepsis definitions (Sepsis-3)^[13]^ with an onset < 24 hours are eligible for study inclusion. A summary of all inclusion and exclusion criteria for participants are provided in Table 1.

**Table 1 T1:**
[figure not shown]
Inclusion and exclusion criteria of Next GeneSiS-trial.

### Interventions

2.3

None.

### Outcomes

2.4

For the evaluation of NGS-performance (sensitivity, specificity, positive predictive value, negative predictive value), results of the NGS-based approach for each sample will be compared with those obtained using conventional microbiology methods for the same sample. Moreover, interobserver agreement will be assessed by the calculation of Cohens Kappa.

The clinical value of the NGS-based approach will be estimated by a panel of 3 independent clinical specialists not associated with the study site, retrospectively identifying potential changes in patients’ management based on NGS results. Therefore, the panel will be provided with clinical case summaries, NGS results, and standard-of-care results from all samples tested. Results of microbiological routine diagnostics in specimens different from blood [e.g., body fluid, tissue, bronchoalveolar lavage fluid (BALF), endotracheal aspirate] will be included when they have been obtained within a timeframe of ≤72 hours prior or after the timepoints for NGS-based measurements. To identify potential changes in antimicrobial management that may have occurred if the results from the NGS technology had been available for clinical use, the panel will be provided with a special questionnaire.

Secondary subgroup analyses will focus on the clinical value especially for patients suffering from a failure of empiric treatment within the first 3 days after onset [as assessed by death of the patient or a lack of improvement of the patient's clinical condition (in terms of an inadequate decrease of SOFA-score) or persistent high procalcitonin levels].

### Description of the used methods

2.5

#### Standard-of-care microbiological analyses

2.5.1

Standard-of-care microbiological analyses of potential pathogens in the different specimens (also including rare pathogens of opportunistic infections in immunocompromised patients such as *Aspergillus* spp., *Mucorales*, *Pneumocystis jirovecii*, *Cryptococcus neoformans*, etc.) will be performed according to the usual practice in each participating institution.

Blood culture testing in Heidelberg University Hospital is routinely performed as described in.^[14]^ In brief, whole blood samples are obtained via direct venipuncture (e.g., antecubital vein) applying sterile techniques and 10 mL blood is inoculated to both an aerobic and an anaerobic liquid culture medium (BACTEC PLUS, BD Biosciences, Heidelberg, Germany). Cultures are incubated for at least 5 days (BACTEC, BD Biosciences, Heidelberg, Germany) and positive cultures are analyzed according to approved inhouse hospital standard techniques, including identification by VITEK2 (Biomerieux, Nuertingen, Germany) or MALDI TOF (Bruker, Madison, WI) and automated antimicrobial susceptibility testing (VITEK 2). Quantification of HSV1 DNA and cytomegalovirus DNA from plasma or tracheal secretion is performed via quantitative real time PCR as previously described.^[15]^ Cultivation of wound swabs, catheter, and stool samples is carried out as previously described.^[16,17]^

#### Next-generation sequencing (NGS)

2.5.2

NGS-based measurements will be performed as described previously.^[11]^ In detail, plasma samples for NGS will be prepared from EDTA-anticoagulated blood tubes (Sarstedt S-Monovette 9 ml K3E) by centrifugation for 10 minutes at 2500*g* (according to manufacturer's instructions) and further storage in Eppendorf tubes (with a plasma volume of 1 ml in each tube) at −80°C until further processing. Plasma sample preparation (starting with the initial blood draw until storage of plasma samples at -80°C) should take no longer than 4 hours. Transfer of plasma samples to Fraunhofer IGB (Stuttgart, Germany) needs to be performed on dry ice. At Fraunhofer IGB, nucleic acids will be isolated from thawed plasma after a centrifugation step of 10 minutes at 16,000*g* with the QIAsymphony sample preparation (SP) instrument and the QIAsymphony DSP Circulating DNA Kit (Qiagen, Hilden, Germany) according to the manufacturer's protocol. Plasma volumes after centrifugation will be adjusted if necessary to 1200 μL with sterile phosphate buffered saline. Final elution of the nucleic acids from the spin column will be carried out with 60 μL molecular biology grade water (5 Prime, Hilden Germany). Contamination controls will be prepared following the same procedure, starting from 1200 μL molecular biology grade water (5 Prime, Hilden, Germany) and 1200 μL of sterile phosphate buffered saline, which will be prepared using the Circulating Nucleic Acid Kit (Qiagen, Hilden, Germany). The cfDNA will be quantified with the Qubit dsDNA HS Assay Kit (Life Technologies, Carlsbad, CA) and quality will be assessed with the HS NGS.

#### Fragment analysis kit and the fragment analyzer instrument (AATI)

2.5.3

Libraries for NGS are prepared from 1 ng cfDNA using the Nextera XT library preparation Kit (Illumina, San Diego, CA) according to the manufacturer's protocol, with a Biomek FXP liquid handling robot (Beckman Coulter, Brea, CA). The final elution will be carried out in 35 μL of resuspension buffer (Illumina, San Diego, CA). A further contamination control is added by using 5 μL of molecular biology grade water (5 Prime, Hilden, Germany) as template for the Nextera XT Library Preparation Kit (Illumina, San Diego, CA). Sequencing of the libraries are performed on a HiSeq2500 (Illumina, San Diego, CA), resulting in 25 to 30 million 100-bp single end reads, on average, per sample. Raw reads are cleared from potential adapter contamination, quality controlled, and, if necessary, trimmed using BBDuk (https://sourceforge.net/projects/bbmap/). To pass the quality filter, read quality needs to surpass a Phred score of 20 and achieve a minimal length of 50 bp after trimming of low quality and adapter bases. Subsequently, NextGenMap is used to align quality-controlled reads to the human reference genome (hg19) requiring a minimum identity between read and reference genome of 80%. Reads mapping to the human reference genome and reads with low complexity (consecutive stretches of di- and trinucleotides along the whole read sequence) are excluded from further analysis.^[18]^ Finally, Kraken is used to assign reads to systematic classification using the RefSeq database (release version 68) comprising 35,749 bacterial and 4340 viral genomes complemented by 12 selected fungal genomes. As several Xanthomonas species are described as well-known contaminants, Xanthomonas reads are excluded as well as the Illumina sequencing spike-in PhiX.^[19]^ To quantitatively compare the number of reads that map to different microbial taxonomic classifications between different samples, the read counts are normalized by the respective library size.

#### Sepsis Indicating Quantifier (SIQ)-score

2.5.4

Within the recently published work,^[11]^ we introduced the n × (s + 1) dimensional count matrix D, where n is the number of control samples and s the number of species detected in all samples. Thus, D_ij_ defines the number of reads found in control sample i for species j. D_i,(s__+__1)_ defines the number of reads which cannot be assigned to any species. One notes that D_i,(s + 1)_ is usually larger than the D_ijs_. Then, Eq. 1 is the maximum likelihood estimate of the probability to observe species j in a control sample:

As the number of reads for 1 species is typically low, we assumed that the read counts for species j are Poisson distributed with parameter:

To test this assumption for each species, a standard χ^2^ goodness of fit test is performed. For reads sequenced from patient plasma, the same data processing pipeline is applied, which yields a read count vector C = (C_1_, …, C_s_, C_s + 1_). On the basis of the Poisson distribution with species-specific parameter λ_j_, the *P* value to observe at least C_j_ read counts in a patient sample is computed as:

If this *P* value is small, then one would reject the hypothesis that the read count of species j in the patient sample follows the Poisson distribution derived from the healthy individuals and conclude that the respective species occurs too often in the patient. Now, with the given species specific λ, we can compute the SIQ score as follows:

The SIQ score now gives rise to a quantitative and probabilistic assessment of every detected microbe in the respective sample.

### Data collection

2.6

The following baseline data will be collected upon enrolment: patient demographics (e.g., age and sex), date and time of hospital and ICU admission, admission source (e.g., emergency department, outpatient clinic/referral, operating room, postanesthesia care unit, and other hospital unit), major comorbid conditions, immune status (host factors predisposing for an immunodeficiency according to^[20]^; *see Supplemental File 4*), site of suspected or confirmed infection, antimicrobial course before study enrolment, surgery/procedures for suspected site of infection before enrolment, and Sequential Organ Failure Assessment (SOFA) Score. Clinical data collection during admission will include pertinent laboratory data, use of mechanical ventilation, and antimicrobial/antibiotic therapy including duration of therapy, and date of therapy will be initiated and discontinued. Vasoactive therapy, renal replacement therapy, surgical and other procedures for diagnosis/treatment of infection, radiological testing for diagnosis/evaluation of potential infection, indwelling vascular access devices, and vital status will also be recorded. Discharge data will include date of discharge (ICU and hospital), discharge destination (general hospital floor, skilled nursing facility, and home), and vital status at discharge (survival/death).

### Participant timeline

2.7

Two sets of blood cultures (2x aerobic/2x anaerobic) will be collected at study inclusion (=Onset) as well as 72 hours afterwards (=72** **h). In parallel, plasma samples for NGS-based measurements need to be obtained as described previously. Further blood samples for NGS-based measurements can be collected whenever physicians order blood cultures (2x aerobic/2x anaerobic) because of the clinical suspicion of a blood stream infection (BSI) within the first 3 days after study inclusion. Results of microbiological routine diagnostics in specimens different from blood (e.g., body fluid, tissue, broncoalveolar lavage, endotracheal aspirate) will be used for further analyses when they are obtained within a timeframe of ≤72 hours prior or after the timepoints for NGS-based measurements. Clinical data collection and (if possible) PCT measurements will be performed at onset as well as at 72** **hours after study inclusion. The final outcome evaluation of patients will be performed at 28 days. A detailed flow chart of the trial specific procedures, assessments, and visits for participants is provided in Fig. 1.

**Figure 1 F1:**
[figure not shown]
Detailed flow chart of specific procedures, assessments and visits (Spirit figure). PCT = procalcitonin.

### Sample size

2.8

*Next GeneSiS* is performed in terms of an exploratory pilot study and is therefore not statistically powered. We estimate that approximately 500 patients need to be enrolled to enable a reasonable assessment of the performance of the NGS-based approach when compared with standard-of-care microbiology.

### Recruitment

2.9

All adult patients (≥18 years) admitted to the participating centers for the management of suspected or proven sepsis will be considered for inclusion in this prospective study.

### Data collection methods

2.10

All data collected in this trial will be recorded on standardized electronic case report forms (eCRF), which have to ensure full documentation of all patient data required by the study protocol. The investigators are responsible for ensuring that all parts of the eCRFs are filled in correctly.

### Data management

2.11

All protocol-required information collected during the trial must be entered by the investigator, or designated representative, in the electronic case report form (eCRF). The investigator, or designated representative, should complete the eCRF pages as soon as possible after information is collected, preferably on the same day that a trial subject is seen for a trial procedure. Any outstanding entries must be completed as soon as possible. The completed eCRF must be approved by the investigator or by a designated subinvestigator.

The approved eCRF is then sent to IMBI being in charge of the data management within the trial. In order to ensure that the database reproduces the eCRFs correctly, the IMBI accomplishes a double entry of data to the statistical program SAS. IMBI representatives will check completeness, validity, and plausibility of data using validating programs, which will generate queries. All validation rules will be predefined in a data validation plan. The investigator or the designated representatives are obliged to clarify or explain the queries. If no further corrections are to be made in the database, it will be closed and used for statistical analysis. The data will be managed and analyzed according to the appropriate standard operation procedure (SOP) valid in the IMBI. According to §13 of the GCP Ordinance,^[21]^ all important trial documents (e.g., CRFs) are archived for at least 10 years after completion of the clinical trial.

### Statistical methods

2.12

For the evaluation of NGS-performance, results obtained with the NGS technology for each sample will be compared with those obtained using conventional microbiology methods for the same sample. Agreement and concordance will be assessed using a McNemar test and Cohen κ. All percentages and confidence intervals (CIs) for proportions will be calculated using the exact method and are rounded to the nearest percentage. Direct comparison of positive and negative results will be conducted with organism identification for each method (conventional microbiology vs NGS). Coagulase-negative Staphylococcus, xanthomonas, and other common skin contaminants will be annotated as “potential contaminants” for both methods and will be excluded from the overall analysis. Discrepant results between the NGS and culture-based techniques cannot be directly confirmed by an independent method. Two approaches will be used to resolve such discrepancies. In a subset of patients, multiple samples will be collected per standard-of-care. This includes 2 independent fresh venipunctures (left arm vs right arm) or 1 venipuncture and 1 sample collected from an indwelling line. Paired analysis of NGS testing results between these independently collected samples will be conducted to indicate the likelihood of true infection. In addition, independent clinical adjudication (described below) will be performed using all the clinical data collected as part of the study, including standard-of-care microbiology results and NGS results.

The clinical value of the NGS-based approach will be estimated by a panel of 3 independent clinical specialists not associated with the study site by the use of a special questionnaire as described above. Analyses of the reviewers’ independent responses will be performed using a majority rule such that 2 of 3 responses for a given patient determine the outcome for that patient. Afterwards, special subgroup analyses (χ^2^ test for categorical data and further methods of variance analysis for continuous data) will focus on the clinical value especially for patients suffering from a failure of empiric treatment within the first 3 days after onset [as assessed by death of the patient or lack of improvement of the patient's clinical condition (in terms of an inadequate decrease of SOFA-score) or persistent high procalcitonin levels]. In addition, graphs are presented where possible. All statistical tests will be performed using SAS (SAS Institute, Cary, NC). A *P* value of less than .05 will be considered statistically significant.

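### Per-sample accuracy analysis with methods that need independent pairs, although patients are scheduled to give two or more pairs: if pairs are pooled, exact CIs are too narrow and McNemar's test rejects too often

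*Protocol article*

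**What the plan says.** Two sections of the Protocol article set the unit for NGS performance. Section 2.4 (Outcomes), on sensitivity, specificity and the predictive values, says that "results of the NGS-based approach for each sample will be compared with those obtained using conventional microbiology methods for the same sample". Section 2.12 (Statistical methods) repeats it: "results obtained with the NGS technology for each sample will be compared with those obtained using conventional microbiology methods for the same sample".

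Section 2.12 also names the methods: "Agreement and concordance will be assessed using a McNemar test and Cohen κ", and "All percentages and confidence intervals (CIs) for proportions will be calculated using the exact method". The significance level is 0.05.

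Section 2.7 (Participant timeline) sets how many samples a patient gives: "Two sets of blood cultures (2x aerobic/2x anaerobic) will be collected at study inclusion (=Onset) as well as 72 hours afterwards", and "In parallel, plasma samples for NGS-based measurements need to be obtained as described previously". In addition, "Further blood samples for NGS-based measurements can be collected whenever physicians order blood cultures" for suspected bloodstream infection in the first 3 days.

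The only within-patient analysis is in section 2.12: "In a subset of patients, multiple samples will be collected per standard-of-care", and NGS results from those separate draws are compared to help resolve discrepancies with culture. That does not correct a variance. The expert-panel outcome, by contrast, is decided per patient by majority.

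**The concern.** The exact binomial interval, McNemar's test and the usual standard error of kappa all treat each NGS/culture pair as an independent unit. Two or three pairs from one septic patient within 72 h share the infection, the host and the treatment, so their results are likely to be positively correlated. Counting them as independent overstates the information in the data.

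NGS performance is the primary objective, and with no formal power the estimates and their intervals are the main product of the study. Intervals that are too narrow, and a P value that is too small, would bear on that product directly. Pooling would also mix onset results with 72 h results, and would give more weight to patients in whom bloodstream infection is suspected again.

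**Working it through.** **Inputs from the document.** About 500 patients (section 2.8); two scheduled pairs each, hence about 1,000 scheduled pairs (section 2.7); significance level 0.05 (section 2.12, taken as two-sided). The Discussion gives 33% for blood-culture positivity, used below only to illustrate an interval.

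**Assumed.** The document gives no within-patient correlation ρ; 0.3, 0.5 and 0.7 are used, with 0.1 as a low value. For McNemar's test, ρ is the correlation of the signed discordance (NGS only, neither, culture only). The McNemar simulation assumes 30% discordant pairs.

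**The plan's own figures.** The 500 has no stated inputs, so it cannot be reproduced, and no error in it is alleged. The nominal 5% can be checked: with one pair per patient the simulated McNemar type I error is 4.8–5.6% (chi-square form) and 3.8–4.6% (exact form), as it should be.

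**Formulas.** With m pairs per patient, the design effect is DE = 1 + (m − 1)ρ. The standard error grows by √DE, the effective number of pairs is 500m/DE, and the true type I error of a nominal 5% test is 2[1 − Φ(1.96/√DE)].

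**Two pairs per patient:**

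| ρ | DE | SE increase | 1,000 pairs worth | McNemar type I error, formula | McNemar, simulated (chi-square / exact) |
|---|---|---|---|---|---|
| 0.1 | 1.1 | 5% | 909 | 6.2% | not run |
| 0.3 | 1.3 | 14% | 769 | 8.6% | 7.9% / 6.9% |
| 0.5 | 1.5 | 22% | 667 | 11.0% | 11.0% / 10.1% |
| 0.7 | 1.7 | 30% | 588 | 13.3% | 13.6% / 12.5% |

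The McNemar simulation used 500 patients and 4,000 runs.

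**Coverage of the nominal 95% exact interval, two pairs per patient, at ρ = 0.3, 0.5, 0.7:**
- 165 patients, 330 samples, true proportion 0.80: 93.1%, 90.9%, 88.8% (96.2% at ρ = 0).
- 335 patients, 670 samples, true proportion 0.70, beta-binomial: 91.7%, 89.4%, 86.9%.

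**Three pairs per patient.** In the first of these set-ups (330 samples, proportion 0.80) coverage is 90.0%, 86.0%, 81.6%. The simulated chi-square McNemar error is 11.4%, 16.7%, 19.3%.

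**Not everyone gives two.** If a share f of patients gives two pairs and the rest one, DE = 1 + 2fρ/(1 + f).
- f = 0.8: DE 1.267 at ρ = 0.3 and 1.444 at 0.5; type I error 8.2% and 10.3%.
- f = 0.6: DE 1.225 and 1.375; type I error 7.7% and 9.5%.

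The same formula serves sensitivity, with f the share of culture-positive patients who are positive at both times. Taking f = 0.25 as an illustration, ρ = 0.5 gives DE = 1 + 0.5 × 0.5/1.25 = 1.2, a standard error about 10% larger.

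**Example.** Sensitivity 0.80 on 330 culture-positive samples (33% of 1,000) has a planned exact interval of 0.753–0.842. Dividing the sample number by the full two-pair DE gives 0.745–0.847 (ρ = 0.3), 0.741–0.851 (0.5) and 0.736–0.853 (0.7). One pair per patient (165 positives) gives 0.731–0.858.

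**The case against.** The strongest reply is that pooling is inferred. The per-sample sentence can be read as a matching rule: it says which culture result belongs with which NGS result, not that all pairs go into one table. Onset and 72 h are separately labelled, and tables by time point would make the named methods valid. A condensed article may also leave repeat samples to a fuller plan that is not shown.

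This stands in part. A reader might infer that the plan declares the samples independent or states that they are pooled; it does neither. But analysis by time point is not stated either, and it would not place the unscheduled pairs. What the article itself fixes is a per-sample unit together with methods that need independent units.

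Other replies also hold, and limit the point:
- Two pairs per patient is true by schedule only. Section 2.4 counts death within 3 days as treatment failure, so some patients will give one pair.
- For sensitivity a patient counts twice only if culture-positive at both times, so the full two-pair effect does not apply.
- No interval or test is planned for kappa beyond the general wording. Clustering affects its standard error; its point estimate is not shown to be biased.
- The plan rounds to whole percentages. In the example at ρ = 0.5 the interval moves from 75–84% to 74–85%, one point on each side. At ρ near 0.1 the loss is small.
- Performance per sample is a legitimate target for a test used whenever cultures are ordered, so the extra weight of repeatedly sampled patients is a choice of estimand. No bias from it has been quantified.

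**Conclusion.** The point holds conditionally. If pairs from one patient are pooled, as the per-sample wording implies, and results within a patient are positively correlated, the exact intervals for the performance measures are too narrow and McNemar's test rejects too often.

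With two pairs per patient and an assumed correlation of 0.3, 0.5 or 0.7:
- standard errors should be 14%, 22% or 30% larger;
- coverage of the nominal 95% interval is about 92–93%, 89–91% or 87–89%;
- McNemar's type I error is about 8–9%, 11% or 13%.

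These are upper figures for sensitivity and for a cohort in which some patients give one pair; a third pair in many patients would push them up. The direction follows from the methods named; the size rests on a correlation that the document does not give.

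A reader might take this as a flaw that invalidates the study's results. The document does not support that: section 2.8 calls the study exploratory and unpowered, and no performance threshold or confirmatory hypothesis depends on the P value. It should be fixed before analysis.

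**What to change.** State in section 2.12 that the primary performance analysis uses the onset pair, one per patient and about 500 in all. The exact intervals, McNemar's test and kappa are then valid as named. Report the 72 h pair separately, in the same way.

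For any analysis that pools time points or includes unscheduled samples, name a patient-clustered variance: GEE or a patient-level bootstrap for the proportions and kappa, and a clustered McNemar test. Weighting patients equally can be added as a sensitivity analysis; it is optional, because it changes the estimand.

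No new data are needed. The cost is analysis wording, some SAS code, and wider intervals than a naive pooled analysis would show: in the example above, 0.731–0.858 from one pair per patient against 0.753–0.842.

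### Section 2.12 names methods for independent pairs, but compares NGS with culture per sample and does not limit tables to one pair per patient; results pooled within patients would look too precise

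*Protocol article*

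**What the plan says.** All places are in the protocol article.

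- **Unit of comparison.** Section 2.4 (Outcomes), on sensitivity, specificity and the predictive values: "results of the NGS-based approach for each sample will be compared with those obtained using conventional microbiology methods for the same sample". Section 2.12 (Statistical methods) repeats the rule: "results obtained with the NGS technology for each sample will be compared with those obtained using conventional microbiology methods for the same sample".
- **Samples per patient.** Section 2.7 (Participant timeline) says that blood cultures "will be collected at study inclusion (=Onset) as well as 72 hours afterwards", and then: "In parallel, plasma samples for NGS-based measurements need to be obtained as described previously". It also allows more within the first 3 days: "Further blood samples for NGS-based measurements can be collected whenever physicians order blood cultures".
- **Methods.** Section 2.12: "Agreement and concordance will be assessed using a McNemar test and Cohen κ", and "All percentages and confidence intervals (CIs) for proportions will be calculated using the exact method". The significance threshold is P < .05.
- **Size.** Section 2.8 (Sample size) claims no power and gives a number of patients: "approximately 500 patients need to be enrolled to enable a reasonable assessment of the performance".

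The article does not mention within-patient correlation, a single analysed sample per patient, or separate tables for onset and 72 h. The panel analysis in section 2.12 differs: the majority of three reviewers gives one outcome per patient.

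**The concern.** An exact binomial interval, McNemar's test and the usual standard error of kappa all treat each pair as an independent observation. Two NGS/culture pairs taken 72 h apart from one septic patient share the host, the focus, probably the organism and much of the antimicrobial exposure. Positive correlation is therefore to be expected. If both pairs enter one table, the formulas count more information than the patients supplied.

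This bears on the primary objective in section 1.3, the performance of NGS against culture. With no power calculation, the widths of the intervals are the main statement of how well that performance is known.

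**Working it through.** **The plan's own figure.** The 500 patients cannot be reproduced or refuted. Section 2.8 gives no precision target, expected sensitivity or correlation, and the article states no interval width.

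**Inputs from the document.** About 500 patients; 2 scheduled pairs per patient; alpha 0.05; 33% as an illustrative proportion (the blood-culture figure in section 3, Discussion).

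**Assumptions.** The exact method is Clopper-Pearson. Tests are two-sided. Every patient gives m = 2 pairs with exchangeable correlation ICC. The ICC is not in the document and is varied from 0 to 1.

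**Step 1: effective sample size.** Design effect = 1 + (m − 1) × ICC; effective n = 500m / design effect. For m = 2 and a proportion of 70%:

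| ICC | Design effect | Effective n of 1,000 | Naive half-width (points) | Adjusted half-width (points) |
|---|---|---|---|---|
| 0.1 | 1.1 | 909 | 2.9 | 3.0 |
| 0.3 | 1.3 | 769 | 2.9 | 3.3 |
| 0.5 | 1.5 | 667 | 2.9 | 3.55 |
| 0.7 | 1.7 | 588 | 2.9 | 3.8 |
| 1 | 2.0 | 500 | 2.9 | 4.1 |

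At ICC 0.5 the naive interval is 1 − 1/√1.5 = 18% too narrow.

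**Step 2: coverage of the nominal 95% exact interval.** Simulated, 40,000 runs, 500 patients × 2 samples, true proportion 33%:

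| ICC | 0 | 0.05 | 0.1 | 0.3 | 0.5 | 0.7 | 1 |
|---|---|---|---|---|---|---|---|
| Coverage | 95.3% | 94.7% | 93.9% | 92.0% | 89.9% | 87.3% | 83.1% |

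With 165 patients and a true proportion of 90%, coverage is 95.3% at ICC 0.05 and 94.7% at 0.1. There the built-in conservatism of the exact method absorbs the effect.

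**Step 3: McNemar type I error at nominal 5%.** Simulated, 10,000 runs, 500 patients × 2 samples, 30% discordant, no true difference:

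| ICC | 0 | 0.1 | 0.3 | 0.5 | 0.7 | 1 |
|---|---|---|---|---|---|---|
| Asymptotic test | 5.1% | 5.8% | 8.7% | 11.1% | 13.2% | 16.0% |
| Exact test | 4.4% | 5.0% | 7.9% | 10.1% | 12.2% | 14.6% |

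With 10% discordant, the asymptotic figures are 6.4%, 8.7%, 11.0% and 13.2% at ICC 0.1, 0.3, 0.5 and 0.7, so the result hardly depends on that choice.

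**Step 4: sensitivity separately.** Only culture-positive pairs enter the denominator of sensitivity, so a patient contributes twice only if both cultures are positive. Suppose, as an assumption, that 30% of the patients with any positive culture are positive twice. The size-weighted mean cluster size is (0.7 × 1 + 0.3 × 4) / (0.7 × 1 + 0.3 × 2) = 1.9 / 1.3 = 1.46. At ICC 0.5 the design effect is 1 + 0.46 × 0.5 = 1.23, and the interval is 1 − 1/√1.23 = 10% too narrow rather than 18%.

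**The case against.** **Pooling is implied, not stated.** The per-sample wording may only say how an NGS result is matched to its culture. Section 2.7 names two distinct time points, and one table for each would contain one pair per patient, for which the named methods are correct. This stands as a limit on the point: the error arises only where pairs are pooled. It does not remove the point, because section 2.12 fixes a sample-level comparison and methods that assume independence, and says nothing to keep pairs from one patient out of the same table. An analysis plan that followed it literally would pool.

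**The effect may be small.** At ICC up to about 0.1 it is negligible. Even at ICC 0.5, the half-width for 1,000 pairs at 70% grows by less than one point, and section 2.12 rounds to whole percentages. Both facts are correct. The McNemar error, however, does not shrink with sample size.

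**Stronger readings that the document does not support.**

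- A reader might infer that every interval in the study is too narrow. No numerical interval is given, and the panel proportions, which the same sentence on the exact method covers, rest on one outcome per patient.
- A reader might infer that every patient supplies at least two pairs. That is the schedule; section 2.12 itself allows for death within the first 3 days, so some patients may give one.
- A reader might count the left-arm/right-arm or line draws as further clustered pairs. Section 2.12 introduces them for an NGS-versus-NGS comparison to help resolve discrepancies and does not add them to the NGS-versus-culture table.
- A reader might take three pairs per patient as typical. The additional samples are optional and depend on a clinician ordering cultures.

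**Conclusion.** The point holds conditionally. Any performance or agreement result that puts more than one pair per patient into a table and uses the methods of section 2.12 as named would overstate its precision or reject too often. How far depends on a correlation that has to be assumed: for two samples per patient the loss is unimportant at an ICC of 0.05-0.1 and material from about 0.3 upwards. The effect on sensitivity is smaller if few patients are culture-positive at both time points. The estimates of sensitivity, specificity, predictive values and kappa are not affected; only their intervals, standard errors and P values are.

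This should be fixed, but it does not threaten a confirmatory claim: section 2.8 describes an exploratory, unpowered pilot, and no decision rule depends on a P value.

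**What to change.** Add to section 2.12:

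1. Performance and agreement are reported by time point, with one pair per patient in each table (for example, onset as the main table). The exact method, McNemar's test and kappa then apply as named.
2. Any figure that pools pairs within patients uses patient-clustered inference: GEE with robust variance or a patient-level bootstrap for the proportions, a bootstrap of whole patients for kappa, and a clustered McNemar test.
3. Duplicate draws taken at the same time serve the NGS-versus-NGS comparison and are not counted as extra independent pairs.

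The cost is a few sentences and a little code, with no new data. The downside is fewer pairs per table under item 1, or somewhat wider intervals and larger P values under item 2.
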